## Abstract

**Background:** Hallmarks of alcohol use disorder (AUD) are disturbances of circadian rhythms and everyday structures. While circadian rhythms dictate the timing of daily recurring activities such as sleep, activity, and meals, conversely, these activities represent time cues, so called *Zeitgebers*, that the circadian system uses to synchronize with the environment. Here we present a study protocol for our newly developed therapy approach for AUD patients, in which we take advantage of this mutual influence and stabilize and strengthen their circadian system by creating strict daily schedules for daily *Zeitgeber* activities. Since every person has a circadian system with its own characteristics and is subject to social obligations, the daily plans are personalized for each test person. Our hypothesis is that a regular exposure to *Zeitgebers* stabilizes behavioral and physiological circadian rhythms and thereby reduces the risk of alcohol relapses and depressive symptoms and facilitates physical recovery in AUD patients during the 1st weeks of their addiction therapy.

**Methods/design:** The study is a 6-weeks single site trial with a controlled, randomized, single-blinded, parallel-group design including patients with a diagnosis of AUD. The study runs parallel to the standard addiction therapy of the clinic. Patients are randomly assigned to either an intervention group (DAILY) or a sham control group (placebo treatment). Questionnaires and physiological assessments of both groups are conducted before and immediately after the intervention or control treatment. According to our hypothesis, the primary outcomes of this study are improvements of regularity, alcohol consumption, and relapse rate in AUD patients compared to AUD patients receiving control treatment. Secondary outcomes are reduced depressive symptoms and increased physical recovery.

**Discussion:** This study is a randomized controlled trial to investigate the efficacy of a personalized circadian *Zeitgeber* therapy as an adjunctive treatment for alcohol use disorder patients. The overall goal of this and more extended future studies is the development of an adjunctive therapy for AUD patients that is uncomplicated in its use and easy to implement in the clinical and everyday routine.

**Trial registration:** This study is registered at the German Clinical Trial Register with the trial number DRKS00019093 on November 28, 2019.

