## Study Hypotheses and Objectives

Our primary hypothesis is that a regular exposure to *Zeitgebers* stabilizes circadian behavioral rhythms and thereby reduces alcohol consumption and the risk of alcohol relapses in AUD patients. Accordingly, the primary objectives of the study are to determine whether the intervention program DAILY decreases day-to-day variations in behavior and reduces alcohol consumption and the relapse rate in AUD patients compared to those receiving control treatment. Furthermore, we hypothesize that the regular exposure to *Zeitgebers* contributes to the reduction of depressive symptoms and a subjective and physiological well-being in AUD patients, which in turn positively affects the primary objectives of the study. Accordingly, the secondary objective of the study is to ascertain whether the DAILY program supports the surrogate criterions of increased sleep quality, reduced depressive symptoms, increased self-efficacy expectations, and improved blood-values that are associated with harmful alcohol consumption. We also hypothesize, that additional psychoeducation about biological mechanisms in the development of AUD helps participants to complete their current therapy and maintain compliance. Therefore, as exploratory outcomes, we will investigate whether more participants of the intervention group accomplish the DAILY therapy than participants of the control group. Finally, we will assess whether the DAILY intervention has impact on the chronotype of the participants, although it is not a specific aim of our treatment to change it.

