### Informed Consent and Baseline Assessments

To participate in the study, all participants need to sign an informed consent in the 1st week (Figure 1). Afterwards, irrespective of the group allocation, a semi-structured interview is conducted to assess demographical data: age, gender, employment status, occupation, and marital status. Medical data are evaluated as well: size, bodyweight, blood pressure, current medications, and information about previous alcohol problems and possible depressive episodes. In addition, the questionnaires described below (Table 1) are filled out together with the participants. Lastly, blood samples are collected. This appointment is also used to prepare the test persons for the topics and contents of their respective groups.

**Table 1 T1:** Overview of questionnaires, physiological assessments, and time points.

**Assessment category**	**Assessment instruments**	**First session**	**Last session**	**Between sessions**
Baseline	Demographics	x		
Circadian	Sleep-Food-Diary			x
	Munich ChronoType Questionnaire (MCTQ)	x	x	
	Pittsburgh Sleep Quality Index (PSQI)	x	x	
Alcohol use	Alcohol use disorders identification test (AUDIT)	x	x	
	European Addiction Severity Index (EuropASI)	x	x	
	Timeline Followback 30 (TLFB)	x	x	
Depression	Hamilton Depression Scale (HAMD)	x	x	
	Inventory of Depressive Symptomatology (IDS-SR)	x	x	
Self-efficacy	Self-Efficacy Questionnaire (SWE)	x	x	
Blood values	Blood draws	x	x	

The further course of the study and the contents of the following appointments are described separately for the intervention group and the control group.

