#### Weeks 3–6: Self-Employed Application of the Daily Structure Plans, Telephone Appointment, and Final Assessment

Starting from this point in the study, the test persons are asked to independently implement the previously developed daily plan for the next 4 weeks and to continue filling out their diaries. The implementation of the daily structure plan can already start at times when the patients are still on the ward or in the day clinic, as patients are allowed to choose the times of all activities (going to bed, eating, leisure activities) freely, with the exception of the fixed therapy sessions on weekdays (see above). However, many patients are discharged or transferred to another institution at different times during this phase of the study. Patients who are discharged home will be asked to follow up the daily schedule outside the clinical setting. Patients who continue their treatment in other institutions will be asked to maintain their daily schedule as much as possible in their new environment. During this time, they can contact the study staff for further assistance (i.e., to adjust the daily structure plan). After 2 weeks, participants are contacted by the study staff by telephone. The telephone call follows the rules of motivational interviewing (65) in order to motivate and remind the participants to further keep to the agreed daily structure and to continue to fill in the diaries thoroughly. If desired, patients are asked to send already completed diaries by fax, mail, or email. The continuous completion of the diary during the application phase of the study serves not only for continuous data collection but also for self-monitoring and increasing compliance. Another 2 weeks later, a last individual appointment is arranged. During this session, diaries will be collected, the questionnaires from the first session are repeated and another blood sample is taken (Table 1).

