Additionally, a questionnaire specially designed for this study with a total of 30 questions and a 4-step ordinal scale for the answers to assess the rating of the participants' subjective structuredness in their everyday life will be filled out. This questionnaire includes, for example, questions on the subjective assessment of whether activities such as eating, sleeping and sport are carried out regularly, whether relapses are associated with irregular daily routines, and whether the craving for alcohol usually occurs at the same time of day. To give the subjects of the control group no indication of the actual aim of the study, the questions that aim at the circadian daily structure are mixed with neutral questions.

Drinking behavior and daily craving will be assessed with questionnaires and the diary, respectively (Table 1). General drinking habits of the last few weeks are surveyed using the AUDIT questionnaire. In addition, the European Addiction Severity Index (EuropASI) is used, which covers not only alcohol and drug consumption but also physical, psychological, financial, and social problem areas of addicted patients. The number of alcoholic drinks and the number of alcohol-free days within the past 30 days is assessed by means of the Timeline Followback 30 (TLFB-30). The diary, which the subjects fill out to collect the Routine Variability Scores, additionally records the highest craving for alcohol on a scale of 0–10 of each day.

According to our secondary hypothesis that the stabilization of circadian rhythms contributes to the reduction of depressive symptoms and increased well-being, changes in the affective state, with a focus on depressive symptoms, are measured with the external assessment questionnaire Hamilton Depression Scale (HAMD) and with the self-reporting questionnaire Inventory of Depressive Symptomatology (IDS-SR). Sleep quantity and quality will be assessed by Pittsburgh Sleep Quality Index (PSQI). Furthermore, for measuring if the DAILY structure program will influence the feeling of self-efficacy, we will employ the Generalized Self-Efficacy Scale (GSES).

As exploratory outcomes, it will be documented how many subjects in the DAILY intervention group and the control groups discontinue the therapy. Furthermore, possible changes of the chronotypes in the course of the study will be defined by the Munich ChronoType Questionnaire (MCTQ).

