## Data Analysis

All statistical analyses will be performed using SPSS software version 25 (SPSS INC., Chicago, IL, USA). Sociodemographic data, chronotype, diary data and blood parameters will be reported in form of descriptive statistics. Continuous variables will be presented as mean ± *SD* and normality of continuous data will be measured by using the Kolmogorov-Smirnov-Test. Accordingly, we will use parametric and non-parametric analyses. For all calculations, the significance level will be determined at α < 0.05.

Data analysis will be performed according to intention-to-treat analysis (ITT) rules. In particular, this means that all subjects who completed the questionnaires of the first session and the 1st week of the diaries are included in the analysis, regardless of whether their subsequent data sets are complete or whether they have dropped out of the study. This is done by imputing missing data with the help of all available data that was assessed until then. Participants who withdraw their consent and were not assessed with baseline measurements will be treated as dropouts. All other subjects regardless from the study condition will be analyzed according to ITT.

The data will be evaluated in three different ways: First, outcomes of the endpoint of the study will be compared between the intervention and control groups using unpaired group analyses (e.g., Student's *t*-test, Mann-Whitney *U*-test, Kruskal-Wallis test, one-way ANOVA). Secondly, within-subject analyses of the intervention and control groups are performed, comparing the changes between the start and end of the study of the two groups (e.g., two-way ANOVA). Thirdly, the data are calculated independently of group membership in two-dimensional linear regression using the Routine Variability Scores as an independent variant.

Additionally, statistical differences in the frequency of dropouts between the two groups are calculated using chi-square tests and survival analyses. Multiple regression analyses will be applied to investigate the degree to which predictor variables (i.e., Routine Variability Scores, depression level, severity of alcohol consumption behavior, and self-efficacy score) contribute to outcomes of primary and secondary measures.

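### Drinking is measured only at the first and last sessions, so dropouts kept in the analysis have no on-treatment drinking record, and unequal dropout could bias the primary comparison in either direction

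*Protocol article*

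**What the plan says.** The Abstract states that "the primary outcomes of this study are improvements of regularity, alcohol consumption, and relapse rate in AUD patients", compared with control.

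Table 1 (Informed Consent and Baseline Assessments) marks AUDIT, EuropASI and TLFB at the first and last sessions. The Sleep-Food-Diary is the only instrument marked between sessions. Measured Outcomes divides the work the same way: "Drinking behavior and daily craving will be assessed with questionnaires and the diary, respectively". On the TLFB it says: "The number of alcoholic drinks and the number of alcohol-free days within the past 30 days is assessed". The diary contents listed for week 1 of the intervention group are routine times, sleep, mood and craving. Drinks are not among them.

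The section on weeks 3–6 says that at the final appointment "the questionnaires from the first session are repeated and another blood sample is taken". It also provides for a call midway through that phase: "After 2 weeks, participants are contacted by the study staff by telephone". The Control Group section gives the control arm the same procedure and sequence.

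Data Analysis includes everyone who completed the first-session questionnaires and the first diary week, whether or not they drop out later. It does this by "imputing missing data with the help of all available data that was assessed until then". Study Hypotheses and Objectives adds, as an exploratory question, that "we will investigate whether more participants of the intervention group accomplish the DAILY therapy than participants of the control group".

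**The concern.** The assessment schedule and the missing-data rule do not fit together. For a participant who misses the last session, the only drinking data of their own are the first-session answers, and the TLFB answer covers the 30 days before that session. Ward patients enrol after at least 5 days of detoxification, and day-clinic patients are already detoxified. The look-back may therefore mix drinking before admission with abstinence under care. Neither is a post-treatment outcome.

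If dropout were the same in both arms, this would mainly add noise and dilute any effect. The protocol, however, hypothesises that completion is better under DAILY. With unequal dropout, whatever value stands in for the missing outcome enters the two arms in different proportions and creates or hides a difference. Two of the three named primary outcomes are exposed. No imputation model chosen later can recover on-treatment drinking that was never recorded, so the schedule has to be corrected while data are still being collected.

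**Working it through.** The article gives no sample size, dropout rate or relapse rate, so there is no planned figure to reproduce. All rates below are assumptions, chosen to show direction and rough size.

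**1. What a dropout contributes**
- First-session AUDIT, EuropASI and TLFB: present, but pre-treatment.
- First diary week: present, since inclusion in the analysis requires it. It holds craving, not drinks, and precedes the daily plan.
- Later diaries: collected at the last appointment, with earlier return optional, so they may be lost.
- Last-session drinking instruments: absent.

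**2. Drinking days, first-session TLFB used as the end value, no true effect**

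False difference (control minus DAILY) = (control dropout − DAILY dropout) × (baseline mean − end mean).

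Assume 20 drinking days at baseline and 5 at the end in both arms:
- Dropout 30% v 30%: 0 × 15 = 0 days.
- Dropout 30% v 20%: 0.10 × 15 = 1.5 days in favour of DAILY.
- Dropout 40% v 20%: 0.20 × 15 = 3.0 days.
- Dropout 50% v 20%: 0.30 × 15 = 4.5 days.

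The other baseline/end pairs tried were 25/5, 15/5 and 20/10. Over all four pairs and the three unequal dropout patterns, the false benefit runs from 1.0 to 6.0 days.

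**3. Effect on the test at 0.05**

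The article says that 3–5 participants are usually in the study at once. Over one year of 6-week courses this implies about 3 × 52/6 = 26 to 5 × 52/6 = 43 in total, or roughly 13 to 21 per arm. The t-test was simulated with 4,000 runs per setting, assumed SDs of 8 (baseline) and 6 (end), values limited to 0–30, dropout unrelated to drinking, and a two-sided test:

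| Dropout, control v DAILY | 13 per arm | 21 per arm |
|---|---|---|
| 30% v 30% | 0.06 | 0.05 |
| 30% v 20% | 0.08 | 0.08 |
| 40% v 20% | 0.12 | 0.18 |
| 50% v 20% | 0.21 | 0.33 |

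The Mann-Whitney results are similar (0.07, 0.16 and 0.30 for the three unequal patterns at 21 per arm).

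**4. Relapse, dropout 20% (DAILY) v 40% (control), true relapse 30% in everyone**

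Observed rate = (1 − dropout) × 0.30 + dropout × value assigned to dropouts.
- Dropouts scored as abstinent (0): DAILY 0.80 × 0.30 = 24%; control 0.60 × 0.30 = 18%. A false 6 points against DAILY.
- Dropouts scored as relapsed (1): DAILY 0.24 + 0.20 = 44%; control 0.18 + 0.40 = 58%. A false 14 points for DAILY.

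The true difference is zero in both cases. The sign depends only on the value assigned to dropouts.

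**5. Missing = relapsed when dropouts do relapse more**

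With 70% relapse among dropouts and 30% among completers, the true rates are 0.80 × 0.30 + 0.20 × 0.70 = 38% (DAILY) and 0.60 × 0.30 + 0.40 × 0.70 = 46% (control), a benefit of 8 points. Scoring all dropouts as relapsed still reports 14.

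**The case against.** **The imputation method is unnamed, and naming it is commonly left to a fuller document.** This stands, and the missing name is not the point here. The available data could include diary craving and mood after baseline, or other participants' outcomes in a model. A reader might infer that a dropout's outcome is built wholly from pre-treatment information. The text supports that only for the participant's own drinking record.

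**The direction of bias is not known.** This also stands. A reader might infer that the rule erases the relapses that led to dropout and so hides a benefit or a harm. But first-session answers come from patients with alcohol use disorder, often just after detoxification. Carried forward, they could make dropouts look like heavy drinkers. The article also does not say that relapse drives dropout; transfer to another institution is another plausible reason for a missed visit.

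**Unequal dropout is a hypothesis.** It is an exploratory question with no rates attached, and the chi-square and survival analyses of dropout by arm would reveal an imbalance. They would not correct the drinking comparison.

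**The diary form is not shown.** Supplementary Table 1 might include drinks, and Measured Outcomes speaks of relating relapses to irregularity in a given week. The explicit split of drinking to questionnaires and craving to the diary points the other way. This is a residual uncertainty and does not rebut the point.

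**It is a pilot.** The Design section says that proving treatment success is not its main focus. That lowers the consequence, but the outcomes are still named primary and tested at 0.05, and the results are meant to inform a main trial.

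**Conclusion.** The point holds in this form: for anyone who misses the last session, the plan as described yields no on-treatment record of drinking or relapse, yet these participants stay in the primary comparison through imputation. If completion differs by arm, as the protocol hypothesises it may, the comparison can be biased in either direction.

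Under the assumed 20% v 40% dropout and no true effect, the illustrations run from 3 drinking days in favour of DAILY (first-session TLFB carried forward) to 6 percentage points of relapse against it (dropouts scored as abstinent). With equal dropout and no true effect, the false difference is zero. These figures rest on assumed dropout, drinking and relapse rates and on simple stand-ins for an unnamed method, so they are not predictions for this trial.

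The documents do not support a claim that the plan must hide relapses, or that missing = relapsed should replace the planned analysis. Because this is a pilot, the change is advisable rather than critical.

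**What to change.** 1. At the telephone contact already scheduled in both arms, ask for TLFB drinking days and number of drinks since the first session.
2. Try one week-6 call to anyone who misses the final visit, to obtain the TLFB.
3. Use these data in the planned intention-to-treat analysis with imputation.
4. Report missing = relapsed as one bounding sensitivity analysis beside the imputed analysis. It should not be the main analysis, because under unequal dropout it favours the arm with better retention.

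The cost is a few minutes per call and one extra analysis. Two limits remain: a single call will not reach everyone already lost, and answers given by telephone are still self-report.

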## Study Design

### Design

The study is a 6-weeks trial with a controlled, randomized, single-blinded, parallel-group design including patients with a diagnosis of AUD. Patients are randomly assigned to either an intervention group (DAILY) or a sham control group (placebo treatment). As this study represents a pilot randomized trial, which does not primarily focus on proving treatment successes but more on ascertaining the best options for the future main trial, we will include each eligible patient within this year instead of using formal power calculations (64).

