### Study Population

Men and women, unemployed and employed subjects are equally included in the study. Depending on whether the subjects are patients of the ward or day clinic, they are in detoxification or post-detoxification treatment. Study enrollment of subjects who are newly admitted to the detoxification program of the ward will take place at the earliest after 5 days of detoxification, to exclude cognitive and physical limitations caused by acute intoxication and its after-effects. Study participants who are discharged from the ward either go home, receive further treatment in the day clinic, or go to other institutions for long-term therapy. Study participants who are discharged from the day clinic either go home after discharge or go to other institutions for further treatment. The health conditions of all test persons allow them to perform their daily tasks without external assistance. Approximately half of the study subjects have a regular job, while the others are unemployed or retired. Usually 3–5 subjects are involved in the study simultaneously.

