### Allocation

Participants are allocated to either the intervention or control group by a computer-generated randomization list. Each test person is assigned an individual study code, which contains information about the current ward and gender, and otherwise consists of a sequential number. Personal data that could reveal identity and participation in the intervention or control group are not part of the code. The decoding of the code is only allowed for study staff. Until the end of the study, the participants will not be informed about their assignment to the intervention or control group. However, after the end of the study, participants will be informed about their group affiliation and participants of the control group will be given the opportunity to learn about the circadian system and the importance of a structured daily routine.

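### Arms are compared on endpoint values and, separately, on change from baseline, with neither ranked and no baseline-adjusted comparison, although baselines exist for the Table 1 questionnaires and blood values

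*Protocol article*

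**What the plan says.** The Data Analysis section of the protocol article states that "The data will be evaluated in three different ways".

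- **Endpoint.** "outcomes of the endpoint of the study will be compared between the intervention and control groups using unpaired group analyses". The examples are the t-test, Mann-Whitney, Kruskal-Wallis and one-way ANOVA. None has a baseline term.
- **Change.** Analyses described as within-subject, "comparing the changes between the start and end of the study of the two groups (e.g., two-way ANOVA" being the example given.
- **Regression.** Linear regression on the Routine Variability Score, regardless of arm.

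Multiple regressions are added, but arm is not among the predictors listed for them. The choice between parametric and non-parametric tests follows from a check in which "normality of continuous data will be measured by using the Kolmogorov-Smirnov-Test". For every calculation, "the significance level will be determined at α < 0.05".

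Table 1 schedules the sleep, alcohol, depression and self-efficacy questionnaires at the first and last sessions. Table 2 does the same for the blood values. Setting is also on record: under Allocation, each person receives an "individual study code, which contains information about the current ward and gender".

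No sample size is given. The Design section says "we will include each eligible patient within this year instead of using formal power calculations".

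**The concern.** The plan offers two between-arm tests of the same outcome and no rule for choosing between them. They handle baseline in opposite ways. The endpoint test leaves baseline out, so part of any chance difference between the arms at the start carries through to the result. The change test subtracts baseline in full, which over-corrects whenever the correlation is below 1. When they disagree, the article does not say which one answers the question.

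The comparison that weights baseline correctly, ANCOVA, is not named, although the data for it are collected. In a trial likely to have a few dozen patients, the stakes are some avoidable loss of precision and a false-positive rate above the stated level for each outcome.

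**Working it through.** **Inputs.** The article states no sample size, effect size, standard deviation or correlation, so there is no planned figure to reproduce.

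- *Sample size (inferred).* "Usually 3–5 subjects are involved in the study simultaneously". With six weeks each, one year of recruitment and continuous turnover, this gives 3 × 52/6 = 26 to 5 × 52/6 = 43 patients, or 13 to about 21 per arm at 1:1 allocation.
- *Assumed.* Two-sided α = 0.05, standardized difference d = 0.8, equal variances at both visits, no dropout, r from 0.2 to 0.7.

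**Step 1: variance of the arm contrast, relative to endpoint-only (= 1).**

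- Change: Var(Y−X)/σ² = 1 + 1 − 2r = 2(1−r).
- ANCOVA: 1 − r².
- Change relative to ANCOVA: 2(1−r)/(1−r²) = 2/(1+r).

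| r | Change | ANCOVA | Change ÷ ANCOVA |
|---|---|---|---|
| 0.2 | 1.60 | 0.96 | 1.67 |
| 0.3 | 1.40 | 0.91 | 1.54 |
| 0.5 | 1.00 | 0.75 | 1.33 |
| 0.7 | 0.60 | 0.51 | 1.18 |

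Below r = 0.5 the change analysis is less precise than ignoring baseline. Above it, the change analysis recovers much of the available gain.

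**Step 2: power.** The noncentrality is d·√(n/2)/√V, with V from Step 1, referred to the t distribution. At 13 per arm, endpoint-only gives 0.8 × √6.5 = 2.04 against a critical value of 2.06 on 24 degrees of freedom.

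| r | 13 per arm: endpoint / change / ANCOVA | 21 per arm: endpoint / change / ANCOVA |
|---|---|---|
| 0.2 | 50 / 34 / 51% | 72 / 52 / 73% |
| 0.3 | 50 / 38 / 53% | 72 / 57 / 75% |
| 0.5 | 50 / 50 / 62% | 72 / 72 / 83% |
| 0.7 | 50 / 72 / 78% | 72 / 90 / 94% |

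Losing one or two residual degrees of freedom moves the ANCOVA figures by about 0.3 of a percentage point or less. There is a further small cost because covariates are never exactly balanced. The expected variance inflation is about 1 + 1/(2n−4) for baseline alone, which is 1 + 1/22 = 1.05 at 13 per arm. For baseline plus a setting term that explains nothing, it is about 1 + 2/(2n−5) = 1 + 2/21 = 1.10. ANCOVA power at 13 per arm then becomes about 50, 52, 60 and 76% with baseline alone, and 48, 50, 58 and 74% with both terms. At r of 0.2 to 0.3 the gain can therefore vanish.

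**Step 3: chance imbalance.** At 13 per arm the baseline difference between arms has a standard error of √(2/13) = 0.39 SD. The endpoint contrast carries r times that difference and the change contrast carries −(1−r) times it. At r = 0.5, a one-standard-error imbalance shifts the two estimates by 0.5 × 0.39 = 0.20 SD in opposite directions.

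**Step 4: two tests, no ranking.** With no treatment effect, the correlation between the two contrasts is (1−r)/√(2(1−r)) = √((1−r)/2), which is 0.5 at r = 0.5. The bivariate-normal probability that at least one exceeds 1.96 in absolute value is 8.6% at r = 0.2, 9.1% at r = 0.5 and 9.5% at r = 0.8. Simulating 200,000 null trials with 13 per arm gives 8.7, 9.2 and 9.5%.

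**The case against.** The strongest reply is that the plan does use the baselines. The sentence after the endpoint comparison plans a comparison of change, and its group-by-time term is itself a between-arm test. That is correct. A reader might infer that baseline information is thrown away; the document does not support this. At r = 0.7 the planned change analysis already reaches 72% power at 13 per arm, against about 78% for ANCOVA. What remains is that change scores are not the efficient use of baseline, and that two competing tests stand unranked.

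Other stronger readings also fail:

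- *The two-way ANOVA treats a person's two visits as independent.* The section introduces it as a within-subject analysis and gives ANOVA only as an example. A repeated-measures model is the natural reading.
- *The Kolmogorov-Smirnov check will let skewed drinking counts through as normal.* This depends on whether the plain or the Lilliefors-corrected version is used, and the article does not say. Choosing a test from the same data is still a weak rule.
- *Omitting setting biases the comparison.* Randomization protects against that, and the article gives no data on how far setting shifts the outcomes. Adjustment for it is a matter of precision.
- *Every outcome has a usable baseline.* The 30-item structuredness questionnaire has no stated time point. The earliest diary week follows psychoeducation in the intervention arm.

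Finally, this is a condensed article on a pilot whose main purpose is not to prove efficacy, and covariates are often left to an analysis plan. That lowers the weight of the point. It does not remove it, because the article itself states the tests.

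**Conclusion.** The point holds as a recommendation to improve stated methods; it does not show that the planned tests are invalid. The arms are compared twice per outcome, without baseline and on change, with no ranking and no baseline-adjusted comparison.

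The precision gain depends on a correlation that the article does not give. It is negligible at r of 0.2 to 0.3 and about 12 percentage points over either planned test at r = 0.5. At r = 0.7 it is large against endpoint-only but only about 6 points against the change analysis. These figures assume 13 per arm, d = 0.8, 1:1 allocation, equal variances and no dropout. The inflation to about 9% varies little with r, but assumes that a significant result on either test would be read as a finding.

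The conclusion covers the Table 1 questionnaires taken at both sessions and the blood values. It does not extend to the diary-based Routine Variability Score or the 30-item questionnaire.

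**What to change.** For each questionnaire and blood outcome measured at both sessions, name one between-arm analysis: ANCOVA of the final value on arm, the baseline value of the same measure, and setting at enrolment (ward or day clinic). Report the adjusted difference with its 95% confidence interval.

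For skewed drinking counts, fix in advance either a rank-based ANCOVA or a count model such as negative binomial, with the same covariates, in place of a choice driven by the normality test.

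Report within-group change descriptively only. Do not apply this model to the 30-item questionnaire or treat diary week 1 as a clean baseline.

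The cost is two degrees of freedom and a change of wording. At 13 per arm with low r and an uninformative setting term, this could cost about two percentage points of power against endpoint-only (48% against 50% at r = 0.2). No new data are needed, and the models run in SPSS.
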